**5.2 Data Transmission**

The data transmission process was designed with security and efficiency in mind. Each data point was encrypted before being transmitted from the collection site to the central database, ensuring that patient information remained confidential. Secure protocols were used to transfer data over the internet, and access to the database was restricted to authorized personnel only. Regular audits were conducted to monitor data integrity and to ensure compliance with the study's data management plan. Any discrepancies or anomalies identified during the audits were promptly investigated and resolved to maintain the quality of the dataset.

**5.4 Data Storage**

Data storage was carried out using a state-of-the-art database management system that provided robust data backup and recovery solutions. The system was configured to automatically back up data at regular intervals, reducing the risk of data loss due to hardware failure or other unforeseen events. Access to the stored data was strictly controlled through a combination of user authentication and role-based access permissions, ensuring that only authorized personnel could retrieve or modify the information. Furthermore, the database was designed to be scalable, allowing for the seamless integration of additional data as the study progressed. To further safeguard the integrity of the data, a comprehensive audit trail was maintained, documenting all access and changes made to the dataset. This enabled full traceability and accountability for all data-related activities.

**5.5 Data** **Sharing**

Data sharing was conducted in accordance with the highest ethical standards and the study's data sharing policy. Only de-identified data were shared with external collaborators to protect participant privacy. A formal data sharing agreement was established with each collaborator, outlining the terms of data use and ensuring that the data would be used solely for the purposes of the study.

**5.6** **Cancellation of Participation**

In the event of a participant's decision to withdraw from the study, all personal data associated with that individual was immediately removed from the active database. The process was designed to be swift and secure, ensuring that no further use of the participant's information could occur. The participant's data was then archived in a separate, secure location, accessible only for the purpose of maintaining records of the study's conduct and for any follow-up required by the study protocol. This procedure was in place to respect the participant's choice and to maintain the integrity of the research data.

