| **Main Exclusion Criteria** | 1. Patients with a history of psychiatric disorders or cognitive impairments that would interfere with the ability to comply with the study protocol.  2. Patients who have undergone previous elbow surgeries or have other medical conditions that could affect elbow function.  3. Pregnant women or those planning to become pregnant during the study period.  4. Individuals with known allergies to any of the medications or materials used during the surgical procedure.  5. Patients who are participating in other clinical trials simultaneously or have done so within the past 6 months. |
| **Allocation** | Eligible patients were split into two groups by admission time: the control group (56 patients enrolled from Jan.–Jun. 2021) and the WeChat group (56 patients enrolled from Jul.–Dec. 2021). |
| **Statistical Methodology** | The statistical analysis was conducted using SPSS software version 26.0. The primary outcome measures were elbow range of motion (ROM), which were assessed at baseline, at discharge, and at 1, 6, and 12 weeks post-operation. Secondary outcomes included quality of life, elbow function, and postoperative complications. The data was analyzed using descriptive statistics to summarize the demographic and clinical characteristics of the participants. Inferential statistics, including t-tests for continuous variables and chi-square tests for categorical variables, were used to compare the differences between the control and WeChat groups. Repeated measures analysis of variance (ANOVA) was conducted to evaluate the changes in ROM over time within each group and between the groups. The significance level was set at p<0.05 for all statistical tests. |
| **Safety** | Adverse events will be summarized for each group. The safety analysis will focus on the frequency and severity of any complications that arise during the study period. This includes, but is not limited to, infections, allergic reactions, and any other unexpected medical events that may occur. The safety data will be analyzed to determine if there is a significant difference in the incidence of adverse events between the control and WeChat groups. The results will be reported in accordance with the CONSORT guidelines for randomized controlled trials, ensuring transparency and completeness of the safety data. |

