**3.4 Early Withdrawal of subjects**

(1)The study protocol included provisions for early withdrawal of subjects if they experienced any adverse events or if their condition worsened.

(2) Participants were also allowed to withdraw from the study if they felt uncomfortable or dissatisfied with the progress of their rehabilitation or the study procedures.

(3) The research team closely monitored all subjects for any signs of distress or complications that might necessitate an early termination of their involvement in the study.

(4) In such cases, the participants were immediately assessed by a medical professional, and appropriate action was taken to ensure their safety and well-being.

(5) The study protocol was designed to prioritize the health and comfort of the participants over the collection of data, reflecting the ethical standards of the research institution.

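### Section 5.6 bars further use of data from participants who choose to withdraw, while section 3.4 allows withdrawal for outcome-related reasons, so range-of-motion and complication data already collected can be lost selectively

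*Protocol*

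**What the plan says.** Section 3.4 describes three routes out of the study. Its first item refers to "provisions for early withdrawal of subjects if they experienced any adverse events or if their condition worsened" and does not say who takes the decision. The second is the participant's own choice: "Participants were also allowed to withdraw from the study if they felt uncomfortable or dissatisfied with the progress of their rehabilitation". The third has the team watching for "signs of distress or complications that might necessitate an early termination of their involvement in the study".

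Section 5.6 governs the data. Its trigger is narrow: "In the event of a participant's decision to withdraw from the study". Its consequence is broad: "all personal data associated with that individual was immediately removed from the active database", with the stated aim of "ensuring that no further use of the participant's information could occur". The record goes to an archive that is "accessible only for the purpose of maintaining records of the study's conduct and for any follow-up required by the study protocol". Analysis is not among those purposes. Under section 3.5, patients who discontinue are not replaced.

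On the outcome side, range of motion (ROM) is primary (section 4.4.1.1). Heterotopic ossification, ulnar nerve symptoms and repeat stiffness are secondary (section 4.4.1.2), and complications are compared by chi-square (section 4.4.3). The Safety row of the Protocol Summary undertakes to tabulate adverse events by group and adds: "The safety data will be analyzed to determine if there is a significant difference in the incidence of adverse events".

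**The concern.** The reasons for leaving overlap with what the trial measures. Someone dissatisfied with progress may well be someone whose motion is not returning, and someone who leaves after a complication carries an event that the chi-square test is meant to count. If such a person chooses to withdraw, section 5.6 takes out of use the later visits that were never made and also the measurements and events already recorded.

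Three things are at stake: the complication comparison, the ROM contrast, and the undertaking to report adverse events by group, which cannot be fully met for a patient whose record may not be used. Loss could also differ between arms. The study is unblinded (section 4.2), the groups were enrolled in successive half-years, and section 4.3.2 says that the control group had less personal interaction. An analysis plan can choose a method for missing data, but it cannot bring back data that the protocol bars from use.

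**Working it through.** **1. Who is covered by the removal rule**

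| Route in section 3.4 | Who decides | Covered by section 5.6? |
|---|---|---|
| Adverse event or worsening (item 1) | Not stated | Yes if the participant decides; otherwise not stated |
| Discomfort or dissatisfaction with progress (item 2) | Participant | Yes |
| Complications leading the team to end involvement (item 3) | Team | Not stated |

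Item 2 alone is enough for the point, because it is participant-initiated, related to outcome, and plainly within section 5.6.

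**2. Complication rate after selective removal (illustration)**

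Let p be the true rate in an arm and w the share of affected patients who withdraw, with nobody else leaving. The observed rate is p(1 − w)/(1 − pw). The limits 8.4% and 47% are the protocol's range for renewed stiffness (section 1.1). The 20% rate and both values of w are assumptions.

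| True rate p | w = 0.25 | w = 0.50 |
|---|---|---|
| 8.4% | 0.063/0.979 = 6.4% | 0.042/0.958 = 4.4% |
| 20% | 0.150/0.950 = 15.8% | 0.100/0.900 = 11.1% |
| 47% | 0.3525/0.8825 = 39.9% | 0.235/0.765 = 30.7% |

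In an arm of 56 with p = 20%, there are 11.2 expected cases. Removing half leaves 5.6 cases among 50.4 patients, which is 11.1%. If the other arm also has a true 20% and loses nobody, the apparent risk ratio is 0.111/0.20 = 0.56 in favour of the arm that lost patients. If both arms lose the same share, both show 11.1% and the ratio is 1: the rates are understated but the comparison is not distorted.

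**3. Mean flexion after selective removal (illustration)**

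- Assume that the affected 20% have 20° less flexion and that half of them leave one arm. The affected share falls from 0.20 to 0.10/0.90 = 0.111. The arm mean moves by −20 × 0.111 − (−20 × 0.20) = −2.2 + 4.0 = +1.8°.
- As an upper bound, suppose exactly the lowest fraction w of a normal distribution is removed. The mean rises by SD × φ(z_w)/(1 − w). With the control SD of 13.6° in the Result row of the Protocol Summary, this gives 1.5° for 5%, 2.7° for 10% and 4.8° for 20%.

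The reported difference in flexion is 10° (95% CI 4.9 to 15.1). Equal removal in both arms would cancel much of any shift.

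**4. Do the reported results show that patients were lost?**

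The sample size of 112 is stated without effect size, SD, power or dropout rate, so it cannot be reproduced. The reported flexion difference is a difference in change: (124.2 − 71.5) − (114.4 − 71.7) = 10.0°. Its CI half-width is (15.1 − 4.9)/2 = 5.1°. Setting this equal to t × √[(sum of the two change-score variances)/n] and solving for n requires the correlation r between baseline and follow-up, which is not given. The result is about 54.5 per arm at r = 0, 46 at r = 0.25 and 38 at r = 0.5. Across all six outcomes the implied n is about 54 to 67 at r = 0 and 34 to 40 at r = 0.5. The intervals therefore show neither loss nor its absence.

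**The case against.** The strongest case on the other side has five parts.

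- **Scope.** A reader might infer that every patient withdrawn for an adverse event or worsening has the record removed. The documents do not support that. Section 5.6 is triggered only by the participant's decision, and nothing says what happens to the data of patients whose involvement the team ends. This objection stands and limits the point.
- **Meaning of the rule.** The record is archived and not destroyed, personal data is undefined, section 5.5 recognises de-identified data as a separate category, and the consent form is not available for review. The rule could be meant for identifiers only. That is hard to reconcile with the stated aim of "ensuring that no further use of the participant's information could occur", but the ambiguity is real and is itself a reason to reword.
- **Section 6 already separates the two.** Sections 6.3.1 to 6.3.7 and the closing paragraph handle poor progress and worsening symptoms by stopping rehabilitation, reassessing and resuming, without ending follow-up, and section 4.4.2 says complications were documented. This is fair. It means that section 3.4 needs to be aligned with section 6; it does not undo section 5.6 for those who choose to leave.
- **No loss is shown.** A reader might infer that the worst outcomes did drop out, that the reported results are biased, or that all 112 patients can no longer be analysed. No withdrawal counts are available, the flowchart is not shown, and controls also had weekly calls after discharge, so differential loss is only plausible. This stands.
- **Analysis-plan matters.** Handling of missing values, analysis sets and the choice of model may sit in an analysis plan that is not shown. The protocol does not say that its repeated measures ANOVA is restricted to complete cases, and nothing here rests on that.

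**Conclusion.** The point holds as a defect in a stated rule. For participants who choose to leave, section 5.6 as worded takes out of use outcome and safety data already collected, and section 3.4 admits reasons for leaving that are tied to the outcomes. If followed, the rule can bias the group comparison, and it conflicts with the by-group adverse event summary and comparison promised in the Protocol Summary.

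The document does not fix the size or direction. The illustrative figures (20% seen as 11.1%, a flexion shift of 1.8°) assume that half of the affected patients in one arm withdraw and nobody else does. Lower or balanced withdrawal shrinks or cancels the effect on the comparison, and loss in the other arm reverses its sign. Whether the rule reaches patients whose involvement the team ends is an open gap in the text, and whether anyone was in fact lost cannot be determined from it.

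**What to change.** 1. Reword section 5.6 so that de-identified outcome and safety data collected up to withdrawal stay in the analysis unless the participant expressly revokes their use. Say what personal data means there, and whether the section applies when the team ends a patient's involvement. Align the consent wording.
2. State in section 3.4 that stopping rehabilitation does not by itself end the 1-, 6- and 12-week assessments or remove data, and reconcile this with section 6. Clinical decisions on halting rehabilitation are unchanged.
3. Count complications observed before withdrawal in the group in which the patient was enrolled.
4. Report withdrawals by group, reason and initiator (participant or team).
5. Where records have already been archived under section 5.6, restore them only where consent allows.

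The cost is protocol and consent wording plus, for archived records, a consent check that may need ethics review because the rule was adopted out of respect for the participant's choice. No new patients or visits are needed.

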**5.7 Researcher Confidentiality**

Researchers involved in the study were bound by strict confidentiality agreements to protect the sensitive nature of the data and the privacy of the participants. These agreements included clauses that prohibited the unauthorized disclosure of any study-related information to third parties. To further enforce these confidentiality measures, regular training sessions were conducted to educate researchers on best practices for maintaining confidentiality and the potential consequences of non-compliance. The study's leadership also implemented a system of checks and balances to monitor compliance with these confidentiality protocols, ensuring that all research activities were conducted with the utmost discretion and respect for participant privacy.

**5.8 Data Retention Period**

All data were stored securely, with access strictly controlled and monitored to prevent unauthorized access or accidental loss.

1. **Safety**

To ensure participant safety and minimize adverse events, we adhere strictly to national and international ethical norms and regulations, guaranteeing that all research practices comply with both ethical and legal standards.

**6.1 Related to the surgical site**

**6.1.1Severe bleeding or hematoma**

If a large amount of continuous bleeding or a significantly enlarged hematoma is found at the surgical incision site during the rehabilitation process, it may indicate that the damaged blood vessels are not well controlled or that new bleeding points have emerged. Continuing rehabilitation may aggravate the bleeding situation and affect wound healing and joint function recovery.

**6.1.2The aggravation of wound infection**

It is manifested as obvious redness and swelling around the wound, intensified pain, fever, and purulent secretions oozing out, etc. At this time, the body's immune system is mainly focused on fighting the infection. Continuing rehabilitation may lead to the spread of the infection, aggravate the condition and delay healing.

**6.1.3 Structural instability such as fractures or joint dislocations**

It is manifested as obvious redness and swelling around the wound, intensified pain, fever, and purulent secretions oozing out, etc. At this time, the body's immune system is mainly focused on fighting the infection. Continuing rehabilitation may lead to the spread of the infection, aggravate the condition and delay healing.

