**6.3.7 Persistent dizziness or fainting**

If a patient consistently experiences dizziness or fainting spells during rehabilitation sessions, this could indicate a serious issue such as dehydration, low blood pressure, or other cardiovascular problems. Rehabilitation should be stopped, and the patient should be evaluated by a healthcare professional to determine the cause and appropriate course of action.

If have the situations above, the rehabilitation should stopped and change the treatment. In cases where rehabilitation must be halted, it is essential to reassess the patient's condition and modify the rehabilitation plan accordingly. This may involve consulting with specialists, such as endocrinologists for blood sugar issues or mental health professionals for psychological concerns. The revised rehabilitation program should be tailored to the patient's current health status and should only resume once the underlying problem has been resolved and it is deemed safe to do so by a healthcare provider. Regular monitoring and communication with the patient are key to ensuring that the rehabilitation process remains effective and safe throughout the patient's recovery journey.

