During this phase, the range of motion and the intensity of the passive motions may be adjusted based on the patient's progress. The therapist may increase the flexion and extension angles slightly, but still within a comfortable range for the patient.

1. Assisted elbow flexion and extension motions:

The assistance provided in this phase is reduced as the patient's strength and control improve. The focus is on refining the movement pattern and increasing the patient's confidence in using the elbow.

1. Active elbow flexion and extension motions:

The patient continues to perform these movements independently, but now with more strength and control. The number of repetitions may be increased, and the patient can start to add a slight resistance by using a light elastic band if possible.

1. Forearm rotation exercises:

Similar to the first phase, but the speed and range of rotation can be increased to further enhance the forearm's rotational ability.

3)The third phase (12 weeks to 1 year post-operative):

The exercises are the same as the second phase in terms of types. However, strength training is introduced. For example, the patient can use light weights starting from 1kg. In the passive elbow flexion and extension motions, the therapist may apply a gentle force against the movement to challenge the joint stability and muscle strength. During the assisted and active motions, the use of weights can be incorporated to make the movements more challenging. For the forearm rotation exercises, weighted cuffs can be used to increase the resistance during rotation. This phase aims to build muscle strength and endurance to support the long - term functionality of the elbow joint. As the patient progresses, the weight can be gradually increased under the supervision of a healthcare professional.

1. Rehabilitation - related Attention
2. The patient should be monitored closely for any signs of pain or discomfort during these exercises.
3. It is crucial to ensure that the patient does not overexert themselves, as this could lead to setbacks in the recovery process.
4. The therapist will provide guidance on proper form and technique to prevent injury and to maximize the effectiveness of the exercises.
5. Regular assessments will be conducted to track the patient's progress and to adjust the rehabilitation program accordingly.

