**Appendix 3.**

Sample table 1 Contents and characters of Scene-based graphics

| Section | Item | Content | Design feature |
| --- | --- | --- | --- |
| First acquaintance  of elbow | **·**Dissection of elbow | **·**Elbow composition | **·**Anatomical picture and Comic, use different colors present different tissues |
|  | **·**Function of elbow | **·**Range of motion  **·**Daily activity | **·**Arrows to indicate the motion direction and mark the Angle value  **·**Indicate daily activities of elbow by comic |
| Recovery Song | **·**Action points | **·**①ROM exercises^a^  **·**②Strength exercise^a^  **·**③Joint draft^a^  **·**④neurorehabilitation^b^ | **·**Breakdown diagram for each action,  arrows and dotted lines mark motion direction  **·**The location, tools, and frequency of the exercise are represented by comic  **·**Put the rehabilitation formula into the painting, such as "1 loose 2 move 3 ice and 4 fixed, if there is severe pain, do not force." |
|  | **·**Rehabilitation notes | **·**common problem process | **·**indicate by warning symbol |
| Rehabilitation "Double-edged Sword" | **·**Hinged external fixation | **·**instructions of structure, pros and cons,adjustment | **·**Illustrate the function of each component, pros and cons  **·**Adjustment tension and direction marked by cirle and arrow |
| Advance in spite of difficulties | **·**Complications judgment and management | **·**Surgery complications  **·**Rehabilitation complications | **·**Marked by symbols,asnausea,dizziness  **·**Marked by different symbols,as Pin site infection, new onset or exacerbation of ulnar nerve symptoms |

^a^: the motions which should be completed postoperative 0-12 weeks

^b^:the motions which should be completed Postoperative 0-3 weeks

Sample table 2 Study schedule and process for daily class

| Study schedule | | | | | |
| --- | --- | --- | --- | --- | --- |
| Stage | Contents | | | Correspond block | |
| Preoperative 1 day | **·**Elbow anatomy and function | | | **·**First acquaintance of elbow  **·**Advance in spite of difficulties | |
| Postoperative 1 day | **·**Hinged external fixation introduction  **·**Action points (Postoperative 0-3 weeks 1) | | | **·**Rehabilitation "Double-edged Sword"  **·**Recovery Song | |
| Postoperative 2 day | **·**Pain coping 1  **·**Action points (Postoperative 0-3 weeks 2) | | | **·**Advance in spite of difficulties  **·**Recovery Song | |

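### The stop criterion for fracture or dislocation (Section 6.1.3) carries the wound-infection text, and Appendices 2 and 3 time strength exercise differently

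*Protocol*

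**What the plan says.** **Stop criterion.** Section 6.1 of the protocol lists three surgical-site reasons to halt rehabilitation: bleeding or haematoma (6.1.1), worsening wound infection (6.1.2), and "6.1.3 Structural instability such as fractures or joint dislocations". The text under the third heading opens with "It is manifested as obvious redness and swelling around the wound, intensified pain, fever, and purulent secretions oozing out, etc" and ends with the reason for stopping: "Continuing rehabilitation may lead to the spread of the infection, aggravate the condition and delay healing". After the last item of Section 6.3 (6.3.7), a closing rule covers the situations listed before it: "If have the situations above, the rehabilitation should stopped and change the treatment".

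**Strength exercise.** Appendix 2 sets out a one-year programme in three phases. Of the last, 12 weeks to 1 year, it says: "The exercises are the same as the second phase in terms of types. However, strength training is introduced". In its second phase (6 to 12 weeks) the nearest element is optional slight resistance from a light elastic band. Its first phase (day 1 to 6 weeks) has no resistance element. Appendix 3, Sample table 1, describes the content of the scene-based graphics. It lists strength exercise with footnote a, which reads "the motions which should be completed postoperative 0-12 weeks". The Introduction (Section 1.1) adds weight-bearing practice in the functional phase, from 3 months to one year.

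**The concern.** These are operative passages. Section 6.1.3 is one of three surgical-site criteria that trigger a halt. A member of staff who turns to it for fracture or dislocation finds no sign by which to recognise either, and finds signs that point to a different event. The rationale for stopping is equally misplaced.

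The timing question matters because all outcome visits fall at 1, 6 and 12 weeks, inside the window on which the two appendices disagree. Appendix 3 describes the WeChat group's material. According to the Protocol Summary, controls received no scene-graphics education. A reader therefore cannot tell from the protocol what strength content belonged to the period before the last visit, or whether it was the same in both arms.

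**Working it through.** No sample size, error rate or event figure is involved, so the check sets the passages side by side.

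**1. Section 6.1.2 against Section 6.1.3**

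| Sentence | 6.1.2 (wound infection) | 6.1.3 (fracture, dislocation) |
| --- | --- | --- |
| 1 | Local and systemic signs of infection | Identical |
| 2 | Immune system occupied with the infection | Identical |
| 3 | Risk that the infection spreads | Identical |

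Three of three sentences match, and none of the three concerns fracture, dislocation or instability. Text extraction, redaction or an amendment log does not explain this: both headings are present and distinct, and both bodies are complete.

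**2. Does the stop rule survive?** Yes. The heading of 6.1.3 names the condition, and the closing rule in 6.3.7 applies to every situation listed above it. What is missing is the description.

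**3. Windows for strength exercise**

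| Source | Content | Weeks after surgery |
| --- | --- | --- |
| Appendix 3, footnote a | Strength exercise | 0 to 12 |
| Appendix 2, first phase | No resistance element | 0 to 6 |
| Appendix 2, second phase | Optional light elastic band | 6 to 12 |
| Appendix 2, third phase | Strength training introduced | 12 to 1 year |
| Introduction, functional phase | Weight-bearing added | 3 months to 1 year |

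Read literally, the Appendix 3 window (0 to 12) and the third phase of Appendix 2 (from 12) meet only at week 12. If the elastic band is counted as strength exercise, the sources agree over weeks 6 to 12, which is 12 − 6 = 6 of the 12 weeks. Weeks 0 to 6 still have no counterpart in Appendix 2.

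**4. Does the conflict separate the arms?** Section 4.3.1 says the WeChat group's education materials were the same as the control group's and were then turned into a comic. If so, the strength content came from a shared source and differed in format only. The control group's online manual is not reproduced, so its timing of strength work cannot be checked. A difference between the arms is possible but not shown.

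**The case against.** The strongest reply is that both defects are matters of wording with limited reach.

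- **Section 6.1.3.** The heading and closing rule still require a stop. Section 6.3.1 halts the plan when joint movement falls sharply and pain increases. Section 3.4 provides for immediate medical assessment when complications might end participation. Section 4.4.2 has experienced orthopaedic surgeons carry out the assessments and manage adverse events. This stands as partial cover. It does not supply the missing description: Section 6.3.1 attributes the change to an unsuitable method or new lesions inside the joint, not to instability.
- **Strength exercise.** Appendix 3 does not define the term. Footnote a is shared with range-of-motion exercises and joint draft, so it may be an outer window and not a start date for each item. Sample table 2 stages the action points at 0 to 3, 3 to 6 and 6 to 12 weeks, and strength work might sit in the last stage. This narrows the conflict. It does not remove it, because Appendix 2 says of the phase after week 12: "However, strength training is introduced".
- **Timing of the correction.** Enrolment ran through 2021 and results are already in the Protocol Summary, so new wording cannot alter conduct. That is true. The record can still be corrected, and what was taught can still be confirmed.

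A reader might also infer that fractures or dislocations were recorded as infections. The documents do not support this. Section 6 gives reasons to halt rehabilitation and is not a scheme for coding events. Complications are categorised separately in Section 4.4.1.2.

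**Conclusion.** Both inconsistencies are real and visible on the page. Section 6.1.3 has a heading without matching content: one of three surgical-site stop criteria carries the signs and rationale of another. The appendices disagree on when strength exercise belongs, over all of weeks 0 to 12 on a literal reading, or over weeks 0 to 6 if the elastic band counts as strength exercise.

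The consequences should not be stretched. It would be tempting to say that the passages cannot be followed, but the instruction to stop remains in force. It would also be tempting to say that the range-of-motion contrast is affected, but the protocol states that source materials were shared and shows no difference in exercise content between the arms. Nor do the documents say that earlier strength work is harmful. No effect on an estimate, an analysis or the sample size follows from this point, and no size can be calculated.

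The conclusion assumes only that the text shown is current. It takes no view on which timing or which signs are correct.

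**What to change.** 1. The responsible clinicians should replace the copied body of Section 6.1.3 with content that matches its heading.
2. They should check whether the same text was copied into the consent form. The table of contents lists a part of the consent form under the same surgical-site heading, but those pages were not available here.
3. They should reconcile footnote a of Appendix 3 with the second and third phases of Appendix 2 and with the Introduction, and state what the strength exercise item covers.
4. The sponsor should confirm from the comic material and the control group's manual what exercise content each arm was taught before week 12, and record the answer.

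The cost is a wording correction and a short comparison of two sets of existing teaching material. No new data and no change to the analysis are needed. The choice of signs and timing rests with the clinicians.
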